### Adverse event reporting during the interviews

We anticipate that there will be minimal adverse events that are directly related to the study—mainly psychological distress resulting from answering the questions during the survey or loss of private data. However, in the event that we realize any severe form of distress, or loss of privacy/confidentiality, then we will report it promptly reported to the Makerere University school of Medicine Ethics Research Committee (SOMREC) and Uganda National Council for Science and Technology (UNCST).

### Community tracing

In the event that a participant cannot be accessed for the second interview after the baseline one, then, we will ask the VHT to visit the physical location and find out the reason for non-response. The VHT will be provided with a Log to record this kind of information which could be loss of a phone and change in phone number of withdrawal from the study among other reasons. If the participant cannot be contacted on phone and physically (may have moved house), then we will consider this a loss to follow-up.

### Sample size and statistical considerations

#### Hypothesis

We hypothesize that (a) the MHL levels are low in our communities in comparison to those observed in high income countries, (b) a psycho-education intervention delivered by VHTs will lead to a 50% increase in MHL levels in the intervention arm compared to the control arm (that this difference will be clinically important), (c) more participants in the intervention arm will contact our study team compared to the control arm—and that this difference will be clinically important, and (d) it will be cost effective to implement the intervention.
Sample size for the baseline prevalence of study outcomes. We will use the Leslie-Kish formular for calculating the sample size for cross sectional studies.

The formula states that *n* = Z^2^ p (1-p)/E^2.^ (i); n is the sample size, (ii) E is the standard error (5%), (c) - is the standard normal deviation of 1.96 corresponding to 95% confidence interval, (d) p is the proportion of participants, 50%. The prevalence was estimated at 50% (conservative estimate for outcomes or effects sizes with limited literature to refer to), in this case prevalence of poor MHL in the Ugandan community.

Substituting; *n* = 1.96^2^ X 0.5 X (1-0.5)/0.05^2^
*n* = 384. For the population survey, we will use a community correction effect of 2. Thus, the sample size for the community sample will be 384X2 = 764. We will add a 10% sample size to cater for incomplete data mainly due to failure to complete an interview. Thus, the total sample size will be 840 participants (420 in the control and 420 in the intervention arms).
(b)Sample size for the RCT: To determine the effectiveness of the psycho-education intervention, we have calculated the size of effects that our sample will be able to detect a clinically important difference in MHL level between the intervention and control arms. The nature of the educational intervention makes randomization by clusters (villages) more appropriate in comparison to randomization by individuals or household.

To estimate the number of villages required per arm for a clinically important effect size of 50%, we assume power of 80% at the 95% confidence level, mean MHL score of 14.14 and standard deviation (SD) of 2.19 [42], and cluster size of 35 participants and coefficient of variation of 0.25, which yields ~ 8 villages per trial arm. Therefore, 24 villages (both arms) will be required, thus including up to 840 participants (420 per trial arm). The sample size of 24 clusters with 35 participants in each cluster will provide us with enough power to detect statistically significance difference between the two arms.

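### The trial's power calculation does not hold together: the 0.25 coefficient of variation does not fit the stated SD, 8 villages per arm does not make 24, and the only effect considered is 3.2 SD

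*Protocol article*

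**What the plan says.** Under Hypothesis, the protocol article predicts that "a psycho-education intervention delivered by VHTs will lead to a 50% increase in MHL levels in the intervention arm compared to the control arm" and calls that difference clinically important. The paragraph on the RCT sample size takes the same 50%, adds "we assume power of 80% at the 95% confidence level", and lists a "mean MHL score of 14.14 and standard deviation (SD) of 2.19 [42], and cluster size of 35 participants and coefficient of variation of 0.25". It does not say what the coefficient of variation describes, and it gives no ICC.

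It reports the result as follows: "which yields ~ 8 villages per trial arm. Therefore, 24 villages (both arms) will be required". It then concludes that 24 clusters of 35 "will provide us with enough power to detect statistically significance difference between the two arms", without naming a difference or a power figure for that design.

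Just before this, the same section derives 840 participants separately, from a prevalence survey: 384 people, a correction factor of 2, and 10% for incomplete data.

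**The concern.** This paragraph is the only power justification for the primary outcome, the difference in mean MHL change between arms. Three things in it do not fit together:

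- A coefficient of variation of 0.25 on a mean of 14.14 makes villages differ from one another by more than the whole SD quoted for the score.
- The calculation ends at about 8 villages per arm, but the conclusion drawn from it is 24 villages in total.
- The effect behind the power claim is several SDs, so the claim does not say how the trial would perform for a smaller benefit.

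If the trial finds no significant difference, a reader needs to know which differences the design could have detected. The present text does not allow that to be worked out.

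**Working it through.** **Inputs** (protocol article, RCT sample-size paragraph): control mean 14.14; SD 2.19; 35 per village; coefficient of variation k = 0.25; increase 50%; power 80%; 95% confidence, taken as two-sided 5%. The intervention mean is 1.5 × 14.14 = 21.21 and the difference is 7.07.

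**Step 1. Reproduce the 8.** Hayes-Bennett formula for means, with k as the between-village coefficient of variation:

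c = 1 + (1.96 + 0.84)² × [2 × 2.19²/35 + k² × (14.14² + 21.21²)] / 7.07²

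- Within-village term: 9.592/35 = 0.274
- Between-village term: 0.0625 × (199.94 + 449.86) = 40.61
- c = 1 + 7.849 × 40.89/49.98 = 7.42, rounded up to 8

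This matches the article, so it is very probably the calculation that was done. Almost all of the variance comes from k.

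**Step 2. Compare k with the SD.** Between-village SD = 0.25 × 14.14 = 3.54 (5.30 at the intervention mean), against 2.19.

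- If 2.19 is the total SD, k cannot exceed 2.19/14.14 = 0.155, so 0.25 is impossible.
- If 2.19 is the within-village SD, ICC = 3.535²/(3.535² + 2.19²) = 12.50/(12.50 + 4.80) = 0.72.

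**Step 3. Per arm to total.** 2 × 8 = 16 villages, or 16 × 35 = 560 people. The stated 24 villages equal 840/35, and 840 is the prevalence-survey figure.

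**Step 4. Size of the target.** 7.07/2.19 = 3.2 SD.

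**Step 5. What 12 villages per arm deliver on the stated inputs** (noncentral t, 22 df, variance as in step 1):

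| Increase | Points | Power |
|---|---|---|
| 50% | 7.07 | about 96% |
| 30% | 4.24 | 67% |
| 20% | 2.83 | 39% |
| 10% | 1.41 | 14% |

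Setting c = 12 in the step 1 formula gives a difference detectable with 80% power of 5.05 points (36% of the mean, 2.3 SD).

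**Step 6. The same design with a coherent variance.** Take 2.19 as the total SD. The ICC values are assumptions, because the article gives none. Detectable difference = (2.074 + 0.858) × 2.19 × √[2 × (1 + 34 × ICC)/(12 × 35)]:

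| Assumed ICC | Detectable difference (points) | % of mean |
|---|---|---|
| 0.03 | 0.63 | 4.5 |
| 0.05 | 0.73 | 5.1 |
| 0.10 | 0.93 | 6.6 |
| 0.20 | 1.24 | 8.8 |
| 1 (upper limit) | 2.62 | 18.5 |

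**The case against.** The strongest reply is that nothing here harms the trial. The 8 is not an arithmetic slip, since it reproduces. Going from 16 to 24 villages adds power, and on the stated inputs the design has about 96% power for the effect it names. All of that stands. A reader might infer that the trial is underpowered, and the article does not support that for the 50% target. Nor does 96% contradict the article: the 80% is an input to the 8 per arm, and no figure is claimed for 24 villages.

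A second reply is that the coefficient of variation is not named and might describe variation in cluster sizes. With an effect of 0.5 SD (63 per arm before clustering), that reading gives 63 × [1 + (1.0625 × 35 − 1) × 0.095]/35 = 7.99 villages. But it needs an ICC of about 0.095 that appears nowhere, leaves the mean of 14.14 unused, and conflicts with the stated 50% increase in MHL levels. The between-village reading remains an inference, though a well-supported one.

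Three further inferences are tempting and should not be drawn:

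- **The survey's factor of 2 contradicts an ICC of 0.72.** That factor is a correction for a prevalence estimate and is not stated as an ICC for the continuous score. The two assumptions look uncoordinated, which falls short of a strict contradiction.
- **The 35 per village wrongly counts people who will be lost.** The 840 does include the 10% allowance, but the participant identification step recruits 38 per village, so the article is not clear on this. It also makes no practical difference: c is 7.420 with 35 and 7.424 with 32.
- **With a coherent variance the trial detects about 5%.** This holds only for ICCs of about 0.03 to 0.05. A coefficient of variation of 0.10 also respects the 0.155 limit, but it gives an ICC of 0.42 and about 1.73 points (12%).

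Whether 50% is attainable with printed materials is a matter of judgement. That it equals 3.2 SD is arithmetic.

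**Conclusion.** The point holds as a fault in the figures and reasoning behind the power statement. It is not a shortage of participants. The step from 8 per arm to 24 in total fails on the face of the text and needs no assumption. The clash between the coefficient of variation and the SD rests on reading 0.25 as between-village variation, the one reading that yields 8 from the stated inputs alone. Given that reading, the between-village SD of 3.54 is impossible against a total SD of 2.19, or means an ICC of 0.72 against a within-village SD of 2.19.

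The consequence is for interpretation. On the stated inputs, the difference detectable with 80% power is 5.05 points. With 2.19 as the total SD it is 0.63 to 1.24 points for assumed ICCs of 0.03 to 0.20, and it cannot exceed 2.62. The article gives no basis for choosing between these, so its claim of enough power is informative only for an effect near 3.2 SD.

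**What to change.** Keep 24 villages and 840 people, and rewrite the RCT sample-size paragraph:

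1. State that 12 villages per arm follows from 840/35, and remove the inference in "which yields ~ 8 villages per trial arm. Therefore, 24 villages (both arms) will be required".
2. Name the variance term. Replace the coefficient of variation of 0.25 with an ICC or between-village SD that is compatible with 2.19, and say whether 2.19 is the total or the within-village SD.
3. Give the difference in MHL points detectable with 80% power for 12 villages per arm, over an ICC range stated to be assumed. If 2.19 is the total SD and 35 per village are analysed, the figures are about 0.63 points at ICC 0.03, 0.73 at 0.05, 0.93 at 0.10 and 1.24 at 0.20.
4. Report the 50% target as 7.07 points or 3.2 SD, and do not leave it as the only effect behind the power claim. A detectable difference is not a clinically important one, so any other target needs its own justification.

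The cost is a revised paragraph, with no change to enrolment, number of villages or follow-up.

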#### Data collection and management

Data will be collected on paper and then entered into a centralized, web-based data management scheme using the open source software REDCap™. Once the data has been received, it will be stored and only accessible by study staff using a computer locked password. We will code all the data and delink names that can be used to identify participants.

### Statistical analysis

Objective 1: We will report frequencies and percentages of the study outcomes and their 95% confidence intervals. We will use regression analyses to determine associations between the primary outcome (MHL) and the factors that may be associated with it (demographics, CMD).

Objective 2: An intention-to-treat analysis will be conducted to compare the groups at baseline and within 4 weeks to assess the effects of the intervention on MHL. We will use a Student t test to examine this difference. The dependent variable (MHL) will be calculated as a continuous variable. Independent variables including presence of PD, MDD, GAD, PTSD, or SUD will be presented as continuous and categorical variables. Baseline characteristics of the intervention and control arms will be compared at the 5% level to assess if successful randomization was achieved. Data on potential confounders and effect modifiers, including variables that fail to achieve successful randomization (e.g., socio-demographic parameters) shall be used to control for confounding and effect modification. Between-subject analysis at week 4 will be used to assess the direct effect of the intervention by determining if there is a significant difference between the mean MHL scores in the intervention and control arms. Within-subject analysis will be performed among participants in the intervention arm by applying the Generalized Estimating Equations method on repeated measures data.

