## Methods

### Study design and setting

For the proposed study, we will use an open-label cluster-randomized trial of 24 randomly chosen villages (*n* = 12 intervention and *n* = 12 control) in Kampala (*n* = 15), Wakiso (*n* = 3), Mukono (*n* = 4), and Masaka (*n* = 2) districts. Intervention and control villages are located at least 20 km apart to avoid contamination

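### The between-arm test of MHL in a village-randomised trial is a Student t test with no allowance for village, so its nominal 5% false-positive rate is inflated

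*Protocol article*

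**What the plan says.** Under Study design and setting, the protocol article states "we will use an open-label cluster-randomized trial of 24 randomly chosen villages", split 12 and 12. The sample-size section explains the choice of unit: "The nature of the educational intervention makes randomization by clusters (villages) more appropriate in comparison to randomization by individuals or household". The trial calculation there uses a "cluster size of 35 participants and coefficient of variation of 0.25, which yields ~ 8 villages per trial arm", so it allows for variation between villages. The separate survey calculation also inflates for clustering: "For the population survey, we will use a community correction effect of 2".

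The primary outcome (Study outcomes) is the mean change in MHL between the arms. Under Statistical analysis, Objective 2, the test of the intervention effect is given as: "We will use a Student t test to examine this difference". The same paragraph treats MHL as continuous and describes the week-4 comparison as between subjects, on the mean scores of the two arms. It adds control for confounders and effect modifiers. It reserves generalized estimating equations for within-subject change among intervention-arm participants. It mentions no village summary, village random effect, cluster-robust standard error or design-effect correction for the comparison between arms.

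**The concern.** The sample size treats the village as the unit that carries the information, but the named test does not. In a cluster-randomised trial the arm means differ by chance for two reasons: differences between individuals and differences between villages. An individual-level t test counts only the first source properly. It works with 840 − 2 = 838 degrees of freedom, when only 24 units were randomised and 24 − 2 = 22 are available.

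Correlation within villages is plausible here. Village health team members hand out the materials in their own villages and help to accrue participants there, and neighbours share schooling, services and local information.

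At stake is the validity of the p-value and confidence interval for the primary outcome. A chance difference between two sets of 12 villages could be reported as an effect of the materials, in a trial whose Discussion says that it will guide policy and practice.

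**Working it through.** **Inputs from the protocol article**
- Villages: 24, 12 per arm (Study design and setting)
- Cluster size m = 35, coefficient of variation k = 0.25, mean 14.14, SD 2.19, effect 50%, power 80%, 95% confidence (sample-size section)
- Correction effect of 2, stated for the population survey (sample-size section)
- ICC for MHL or for its change: not given, so a range is assumed

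**Step 1. The plan's own figure.** No formula is named. The usual cluster-trial formula for means with a between-cluster coefficient of variation, reading 50% as a rise from 14.14 to 21.21, gives

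c = 1 + (1.96 + 0.84)² × [2 × 2.19²/35 + 0.25² × (14.14² + 21.21²)] / (21.21 − 14.14)² = 7.42,

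which rounds up to the stated 8 villages per arm. The planned size therefore rests on a formula that counts villages and variation between them.

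**Step 2. True error rate of an unadjusted test.** With equal clusters the design effect is DE = 1 + (m − 1) × ICC = 1 + 34 × ICC. A test that ignores clustering understates the standard error by a factor of √DE. Its true two-sided error rate at nominal 5% is 2 × [1 − Φ(1.96/√DE)].

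| ICC | DE | 1.96/√DE | True error rate |
|---|---|---|---|
| 0.01 (assumed) | 1.34 | 1.69 | 9.0% |
| 0.029 (if DE = 2) | 2.00 | 1.39 | 16.6% |
| 0.05 (assumed) | 2.70 | 1.19 | 23.3% |
| 0.10 (assumed) | 4.40 | 0.93 | 35.0% |

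The second row takes the survey's factor of 2 and solves for the ICC: (2 − 1)/34 = 0.029.

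**Step 3. Check by simulation.** In 10,000 null trials of 12 + 12 villages with 35 people each, the individual-level t test rejected in 9.2%, 16.3% and 23.5% of trials at ICC 0.01, 0.029 and 0.05. A separate run of 4,000 trials at ICC 0.10 gave 35.1%. In the 10,000-trial runs, a t test on the 24 village means rejected in 4.9%, 5.1% and 5.1% of trials at the first three ICCs, so it holds the nominal level.

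**The case against.** **The unit of the test is not stated.** A Student t test on 24 village means would be valid, so the sentence is not wrong in every possible reading. This is fair, and the individual-level reading is an inference. It is still the natural one: the paragraph speaks of a between-subject comparison of mean scores and never mentions village means. If village summaries were meant, the text has to say so. A correction is needed on either reading.

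**Other parts of the plan might cover clustering.** They do not. The generalized estimating equations are confined to repeated measures in one arm. Adjustment for participant-level confounders does not model village correlation or restore the right degrees of freedom. The allowance for clustering in the sample size protects power, not the error rate of a test that ignores clustering.

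**The analysis plan might settle it.** Silence could be left to that document. Here the article names a specific test for the primary comparison, and as it reads, that test does not fit the design.

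**The size is uncertain.** This stands. The factor of 2 belongs to a prevalence estimate and does not enter the trial calculation, and a change score may have a lower ICC than a single score. The 17% is therefore conditional. Even an ICC of 0.01 nearly doubles the error rate.

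**The same flaw might be inferred for Objective 1.** There the article says only "We will report frequencies and percentages of the study outcomes and their 95% confidence intervals". It names no interval method, and a condensed article may leave that to the fuller plan. The text does not show that those intervals ignore clustering.

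**Conclusion.** The point holds for the between-arm comparison in Objective 2. Followed as it naturally reads, the plan gives an invalid p-value and too narrow a confidence interval for the primary outcome. The true error rate is about 9% to 35% for assumed ICCs of 0.01 to 0.10, and about 17% if the survey's correction effect also holds for MHL. These figures assume an individual-level test, 12 villages per arm, 35 people in each and a two-sided 5% level.

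A reader might infer a far higher rate, about 70%, from the trial calculation's coefficient of variation of 0.25. That value implies a between-village SD of 0.25 × 14.14 = 3.54. It leads to an ICC of about 0.72 only if the quoted SD of 2.19 is a within-village SD, which the protocol does not say. If 2.19 is the ordinary SD of scores, the between-village variance (3.54² = 12.5) would exceed the total variance (2.19² = 4.8), which is impossible. The two inputs fit poorly together and are no evidence for an error rate of that size.

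**What to change.** Replace the t-test sentence under Objective 2 with a statement that the comparison between arms accounts for village. Either of two forms is enough:
- a t test on the 24 village-level summaries of MHL change, with 22 degrees of freedom; or
- a linear mixed model on individual MAKS scores with arm as a fixed effect, a village random intercept and a small-sample degrees-of-freedom correction (Kenward-Roger or Satterthwaite).

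Adjustment for the baseline MAKS score, which is already collected, is preferable. Adjustment for district is optional: the protocol uses district to spread the sample of villages and does not say that allocation to arms was stratified by it. Report the estimated ICC with the result.

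The cost is a change of wording, with no extra data or participants. For the same outcome and covariates, the standard error will be larger than the naive one, by about √DE (a factor of 1.16 at ICC 0.01 and 1.41 at a design effect of 2), but it will be valid. Baseline adjustment may recover some of that precision.

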**Methods:**

We will employ a cluster randomized trial design in 24 villages in central Uganda. We will collect baseline data to and document the prevalence of MHL, PD, MDD, PTSD, GAD, and SUD. We will distribute information education and communication materials (IEC) aimed at improving MHL to 420 adult individuals in the intervention arm (*n* = 12 villages). In the control arm (*n* = 12 villages), VHTs will distribute ministry of health COVID-19 information leaflets to 420 participants. Within 7 days of distributing the materials, research assistants will conduct a follow-up interview and assess for the same parameters (MHL, PD, MDD, PTSD, GAD, and SUD). We will use an intention to treat analysis to estimate the effectiveness of the psycho-education intervention.

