### Eligibility criteria

Individuals will be eligible for recruitment if they have been residing in the selected villages for a minimum of 6 months and do not intend to migrate or move/shift residence in the next month after being approached. Individuals will be eligible for recruitment if they are at least 18 years of age. All participants will be required to provide written informed consent. For those who can neither write nor read, the consent form will be read to them by trained research assistants (RA) and they will use a thumb print soaked in an inkpad to provide informed consent. The RA will be graduate level social scientists with experience in data collection.

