(iv) Baseline data collection: At baseline, trained research assistants will collect demographic (age, gender, education level and place of residence) information and administer the Mental health Knowledge Schedule (MAKS) [36] to assess for MHL, Kesler-10 (K-10) [37] to measure PD, the Generalized Anxiety Disorder scale (GAD-7) [38] to assess for GAD, Patient Health Questionnaire-9 (PHQ-9) [39] to assess for MDD, Post-Traumatic Stress Disorder-Primary Care Screen (PTSD-PC) [40] for PTSD, and the Alcohol Smoking and Substance Involvement screening Test (ASSIST) [41] to assess for SUD. This data will be collected from participants in both arms. During the baseline data collection, the IEC materials will be distributed to participants in the intervention arm and the ministry of health (MOH) brochures to participants in the control arm.

(v) The intervention: VHTs will distribute the IEC materials to the 12 intervention villages described above after collection of baseline data and encourage participants to read these materials. In the 12 control villages, VHTs will distribute the MOH brochures that contain information about (a) the signs and symptoms of the COVID-19 and the preventive measures, (b) the fact that individuals may suffer from stress during the pandemic, (c) the sources from where they can get psychosocial help, and (d) the contact details of the research team should they need more information. The information contained in the ministry of health brochures are the current standard of care for community members. The IEC materials will be distributed to individuals who participated in the baseline surveys.

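### Results of screening questionnaires are to be reported as the prevalence and presence of MDD, GAD, PTSD and SUD, although the design yields only screen-positive proportions

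*Protocol article*

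**What the plan says.** The Abstract (Methods) says that baseline data will "document the prevalence of MHL, PD, MDD, PTSD, GAD, and SUD". The last paragraph of the Background repeats the aim for common mental disorders (CMD) as a group.

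Study procedure (iv) names the measures of the four disorders:
- Anxiety is measured with the GAD-7 scale.
- The measures of depression and post-traumatic stress are given as "Patient Health Questionnaire-9 (PHQ-9) [39] to assess for MDD, Post-Traumatic Stress Disorder-Primary Care Screen (PTSD-PC) [40] for PTSD".
- Substance misuse is covered by the ASSIST, which the article spells out as a screening test.

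Two of these four instruments carry the word screen or screening in their own names. Research assistants administer all of them, at baseline and again at follow-up.

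Under Statistical analysis, Objective 1 reports frequencies and percentages with 95% confidence intervals and regresses MHL on demographics and CMD. Study outcomes lists those associations as the secondary outcome. Under Objective 2 the form of the CMD variables is given: "Independent variables including presence of PD, MDD, GAD, PTSD, or SUD will be presented as continuous and categorical variables".

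The article describes no diagnostic interview for the sample, no validation subsample and no adjustment for sensitivity and specificity. It does not use a label such as screen-positive or probable. Study procedure (viii) has research assistants assess participants who call for help, but that is not a diagnosis across the study sample.

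**The concern.** A positive questionnaire is not the disorder. The proportion above a cut-off mixes true cases with false positives and misses false negatives. It equals the prevalence only where the two errors happen to cancel. If the plan is followed as written, the report will state a prevalence of MDD, GAD, PTSD and SUD that the design cannot estimate. The confidence interval around it will reflect sampling error alone.

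The secondary outcome inherits the problem wherever disorder enters the regression as present or absent. The Discussion says the findings will guide policy on integrating mental health services. A planner who reads a prevalence of MDD could take a screening rate for a count of cases.

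The point concerns the four disorders. It does not touch the K-10 as a scale of distress, or the MAKS as the measure of MHL.

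**Working it through.** **The plan's own figure.** The article disputes no accuracy figure because it gives none. Its survey size can be checked, since it sets the sampling error used below. From Sample size and statistical considerations: 1.96² × 0.5 × 0.5 / 0.05² = 384; × 2 = 768 (the article prints 764); 764 × 1.10 = 840, or 768 × 1.10 = 845. The planned 840 reproduces closely enough.

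**Inputs from the document.** N = 840; design effect 2; MHL mean 14.14 and SD 2.19.

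**Inputs assumed.** True prevalence p, sensitivity Se and specificity Sp. The article gives none of them for any of the four disorders. Its 10% in the Background is for psychological distress, and its 50% in the sample size is for poor MHL.

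**Formulas.**
- Apparent prevalence = p·Se + (1 − p)(1 − Sp)
- Positive predictive value (PPV) = p·Se / apparent prevalence
- No net bias when p = (1 − Sp) / [(1 − Sp) + (1 − Se)]
- 95% half-width = 1.96 × √(design effect × apparent × (1 − apparent) / N)

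**One illustration: p = 0.10, Se = 0.80, Sp = 0.90.**
- Apparent prevalence = 0.08 + 0.90 × 0.10 = 0.170
- PPV = 0.08 / 0.17 = 0.47
- Half-width = 1.96 × √(2 × 0.17 × 0.83 / 840) = 0.036
- Interval: 13.4% to 20.6%, which excludes the true 10%. The gap is 7.0 points.

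**Range over Se 0.70 to 0.90 and Sp 0.80 to 0.95.**

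| True prevalence | Lowest apparent (Se 0.70, Sp 0.95) | Highest apparent (Se 0.90, Sp 0.80) |
|---|---|---|
| 5% | 8.3% | 23.5% |
| 10% | 11.5% | 27.0% |
| 20% | 18.0% | 34.0% |

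At 20% with Se 0.80 and Sp 0.95 the result is 0.16 + 0.04 = 20%, so there is no bias. With a stricter cut-off (Se 0.50, Sp 0.97), a true 10% appears as 0.050 + 0.027 = 7.7%, an understatement. Over the tabled range, the prevalence at which the errors cancel runs from 14% to 67%.

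**Regression on presence or absence.** If misclassification is unrelated to MHL, the observed MHL difference is the true one multiplied by PPV + NPV − 1 (NPV is the negative predictive value). In the illustration NPV = 0.81 / 0.83 = 0.976, so the factor is 0.47 + 0.976 − 1 = 0.45. The Background, however, defines MHL partly as the ability to recognise signs and symptoms, so MHL may change how symptoms are reported. A simulation of 2,000,000 people (p = 0.10, MHL mean 14.14, SD 2.19, split at the mean) gave these observed differences:

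| Error pattern | True difference −0.65 | No true difference |
|---|---|---|
| Unrelated to MHL (Se 0.80, Sp 0.90) | −0.29 | about 0 |
| High MHL endorses more symptoms (high/low MHL: Se 0.90/0.70, Sp 0.87/0.93) | +0.17 | +0.46 |
| High MHL gives fewer false positives (Se 0.85/0.75, Sp 0.93/0.87) | −0.56 | −0.26 |

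The association can shrink, change sign or appear from nothing.

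**The case against.** The instruments are named openly as means of assessing for each condition, so an informed reader can see that the results are scale-based. Cut-offs and labels such as probable may sit in a fuller protocol or analysis plan, and their absence from an article is no fault. Continuous forms of the same variables are already planned. The primary outcome is the change in MHL and does not depend on any of this. All of that stands, and it keeps the point small. It does not remove the point, because the article itself states prevalence and presence of disorders; the label is not merely left unspecified.

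A reader might also infer more than the document supports:
- **That prevalence will be overstated.** This needs uncommon disorders and lenient cut-offs. The article gives neither, and its Abstract starts from a high prevalence of CMD in people exposed to disasters. At 20% true prevalence, or with a strict cut-off, the bias can vanish or reverse.
- **That the association between MHL and CMD will be weakened.** This needs errors unrelated to MHL, which the article's own definition of MHL makes doubtful.
- **That the error should be judged against the 5-point margin in the survey sample size.** That margin was set for poor MHL at 50%, not for any disorder.
- **That non-clinician interviewers make matters worse.** The article says "The RA will be graduate level social scientists with experience in data collection" and describes them as trained. Nothing in it shows that they add error, and the calculation does not use interviewer type.
- **That information is lost by categorising.** The plan keeps the continuous scores as well.

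**Conclusion.** The point holds as one of labelling and interpretation, at a minor level. The planned percentages for MDD, GAD, PTSD and SUD are screen-positive proportions, and the article presents them as disorder prevalence. The discrepancy can exceed sampling error: 17.0% reported for a true 10%, against a half-width of about 3.6 points. That size rests entirely on assumed prevalence, sensitivity and specificity. Its direction cannot be known from the document, and neither can the direction of bias in the regression on categorical presence. Objective 1 and the secondary outcome are affected; the between-arm comparison of MHL is not.

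**What to change.** In the Abstract (Methods), the last paragraph of the Background and Statistical analysis, replace prevalence or presence of each of the four disorders with the proportion screening positive (or with probable disorder), at a cut-off prespecified for each instrument. Interpret the MHL regression mainly on the continuous scores that Statistical analysis already plans, with the screen-positive categories in support. State in the conclusions that no diagnosis was made, and leave the direction of any bias open.

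This changes wording and the emphasis of one analysis; it needs no new data and no change to the trial's conduct. The cost is that the trial can no longer claim to have measured disorder prevalence.
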